# Background

## Helminth infections

Worm infections remain a major public health problem, particularly in tropical and subtropical regions, primarily affecting socio-economically deprived populations. It is estimated that over a third of the world’s population is currently infected with helminths (‘parasitic worms’) *(1,* 2). This proposal will focus on soil-transmitted helminths, which are estimated to infect more than a billion people globally and are highly prevalent across sub-Saharan Africa *(2,* 3).

Soil-transmitted helminths are intestinal parasitic worms. Humans are the definitive host. These parasites are rampant in areas where hygienic conditions are poor and environmental features are adequate (e.g. high temperatures, sufficient soil moisture). Infections frequently cause chronic and debilitating disease, mainly in infants, pre-school and school-aged children and pregnant women *(2, 4,* 5).

Humans become infected through ingestion of parasite eggs or penetration of infectious larvae through the skin (2). The adult soil-transmitted helminths can live for years in the human gastrointestinal tract. The most common soil-transmitted helminths are the large roundworm (*Ascaris lumbricoides*), the whipworm (*Trichuris trichiura*), and the hookworms (*Ancylostoma duodenale* and *Necator americanus*).

Morbidity due to soil-transmitted helminth infection and the rate of transmission are related to the number of worms harboured by the host (6). Generally, infections with soil-transmitted helminths have a negative impact on pregnancy and birth outcomes, hamper children’s cognitive and physical development, result in reduced work capacity, and therefore compromise the social and economic development of communities and entire nations *(3, 7,* 8). Recent estimates suggest that globally 807-1221 million people are infected with *A. lumbricoides*, 604-795 million with *T. trichiura*, and 576-740 million with hookworm *(1,* 2). Infections with multiple helminth species are common *(9,* 10). In Africa, it is currently estimated that 44% of soil-transmitted helminth infections are concentrated in just four countries, namely Nigeria, Democratic Republic of Congo, South Africa and Tanzania *(*11). The global burden of soil-transmitted helminthiasis is estimated at 39 million disability-adjusted live years (DALYs), hence similar to the global burden owing to malaria or tuberculosis *(7,* 12).

## Soil-transmitted helminthiasis in Zanzibar

In sub-Saharan Africa, more than 500 million people are infected with at least one species of soil-transmitted helminths *(1,* 3) and multiple species helminth infections are the norm rather than the exception *(9, 13-*15). Zanzibar, where the field work of the current project will be carried out is part of the United Republic of Tanzania and consists of two islands, Unguja and Pemba. On both islands soil-transmitted helminth infections were recognized as an important public health problem already in the early 1990s *(*16). Indeed 85% of the surveyed population and 99% of examined schoolchildren were infected with at least one of the major soil-transmitted helminths *(16-*18). Helminth control programmes have been launched in Zanzibar more than a decade ago, to combat soil-transmitted helminthiasis, schistosomiasis and lymphatic filariasis *(16, 19-*21). However, the burden of soil-transmitted helminthiasis remains elevated. Recent studies revealed an overall prevalence of 49.4% for soil-transmitted helminth infections in school-aged children from the 6 districts in Unguja Island *(*22) and a point-prevalence of 77% in all age groups in Kinyasini village *(*19). *T. trichiura* was found to be the predominant helminth species in school-aged children from all 6 districts of Unguja, reaching a point prevalence of 55.2% in district North A *(*22).

## Control of soil-transmitted helminth infections

In view of the ecological and human determinants governing the transmission of soil-transmitted helminths, the total pre-school and school-aged population in the World Health Organization (WHO) African Region is considered to be at-risk of infection (8). Additionally, pregnant women are a major risk group *(23,* 24). Periodic and repeated deworming with benzimidazoles (albendazole and mebendazole), complemented by basic sanitation and clean water, is considered the most cost-effective approach to control morbidity due to soil-transmitted helminth infections *(1, 12,* 25). The benefits of regular treatment in school-aged children include improvement of iron stores *(*26), growth and physical fitness *(26,* 27), and school attendance *(*28). Women that are treated once or twice during pregnancy are less anaemic, birth weight improved and infant mortality at 6 months decreased *(23, 29,* 30). Periodic deworming campaigns lead by the WHO have focused on schools, because the heaviest intensities of soil-transmitted helminth infections are most commonly encountered in school-aged children, and schools provide convenient and efficient infrastructure for delivery of helminth control interventions *(*31). A resolution urging member states to attain a minimum target of regular deworming of at least 75% and up to 100% of all at-risk school-aged children by 2010 was passed at the 54th World Health Assembly in May 2001 *(12,* 31). However, even if the removal of adult worms from the intestinal tract is the goal of anthelminthic treatment (2), the success of mass-drug administration in highly endemic regions is more accurately measured when evaluating infection intensities *(*32). Infection intensities are usually classified according to thresholds set forth by the WHO *(*33) in high, medium and low, expressed by the number of eggs per gram of stool (EPG). Infection intensities are regarded not only as indicator for the worm-burden in the host but also for the degree of environmental contamination with eggs and hence transmission.

The drugs of choice for the treatment of soil-transmitted helminth infections are albendazole and mebendazole. Due to their good safety profile with rare and generally mild and transient adverse events allows their use also by non-medical personnel, such as school teachers in school-based mass treatment campaigns *(*12). However, even if considered to be broad-spectrum anthelminthics, the drugs have different species-specific efficacies *(2,* 34). Whilst albendazole, administered in a single oral dose of 400 mg is highly efficacious against *A. lumbricoides* and hookworm infections, it is less efficacious in curing *T. trichiura* infections *(*35). The respective cure rates (CR) against these three helminths are 88%, 72% and 28% *(*34). Mebendazole in a single oral dose of 500 mg is slightly more efficacious than albendazole against *A. lumbricoides* and *T. trichiura* with observed CRs of 95% and 36%, respectively *(*34). Unfortunately mebendazole lacks efficacy in curing hookworm infections; the overall CR has been reported at 15% *(*34). Ivermectin is the first-line treatment in programmes to eliminate filarial worms (*Wuchereria bancrofti* and *Onchocerca volvulus*) but is not applied to combat soil-transmitted helminthiasis with the exception of *Strongyloides stercoralis* infections where it shows a good efficacy *(36,* 37). However, the combination of ivermectin and albendazole is reported to a higher efficacy in curing *T. trichiura* infections than the use of albendazole alone *(35,* 38), but in general the treatment of *T. trichiura* infections with the currently available anthelminthic drugs is unsatisfactory.

Rapid re-infection in areas of poverty and poor sanitation, hampers the sustainable control of soil-transmitted helminthiasis *(*10), and there is growing concern about the potential emergence of resistance through the widespread and frequent use of anthelminthics *(39,* 40). The identification of new anthelminthic drugs is hence of major importance.

Another problem in terms of accurate monitoring of soil-transmitted helminth control programmes and of the consistency of the efficacy of anthelminthic drugs is the low sensitivity of the parasitological diagnostic methods *(*40), e.g. of the widely applied Kato-Katz method *(*41). If infection intensities with soil-transmitted helminths are low (e.g. due to regular anthelminthic treatment regimens), this method often fails to detect cases due to the small amount of stool investigated *(42,* 43). Hence, the development of new and more sensitive diagnostic tools is of pressing necessity.

The recently developed FLOTAC method - a multivalent faecal egg-count technique - using up to 1 g of stool for investigation, shows a significantly higher sensitivity to detect helminth infections than the Kato-Katz method *(43,* 44). For an appropriate assumption of the CRs of drug efficacy trials, as well as for future monitoring of transmission control, the FLOTAC might become an important supportive diagnostic tool.

## Helminth control programmes in Zanzibar

Zanzibar serves as an example where long-term helminth control programmes have been implemented with both remarkable success and persistent problems. Studies carried out in Pemba and Unguja in the late 1980s and early 1990s revealed that the prevalence of helminth infections exceeded 85% in all surveyed population groups with a considerable amount of moderate, but only few heavy infection intensities *(16,* 18). Therefore, in 1992, a national plan of action for the control of helminths was implemented by the Ministry of Health and Social Welfare (MoHSW) *(*16). Periodical mass-treatment of schoolchildren with a single oral dose of mebendazole (500 mg) was adopted and portrayed as the most cost-effective strategy for the control of morbidity *(*16). As re-infection intensities were found to reach pre-treatment levels already 6 months after treatment, it was decided to treat the children every 4 to 6 months *(16,* 45). Finally, in 1994, the MoHSW established a national helminth control programme *(*46). Since then, large-scale preventive chemotherapy interventions are regularly carried out at schools and occasionally in whole communities *(*19). Currently, on Unguja, the helminth control programme operates from the Helminth Control Laboratory Unguja (HCLU), which provides, when sufficient donor funds are available, the necessary infrastructure and resources for mass drug administration campaigns targeted mainly towards school-aged children *(*47). From 1995 onwards, schoolchildren were treated on a regular basis with mebendazole (500mg). Mebendazole was replaced by albendazole (400mg) in 2003. Additionally, in the frame of the Programme to Eliminate Lymphatic Filariasis, from 2001 onwards, the whole eligible population was treated annually with ivermectin (200µg/kg) and albendazole (400mg) *(*19).

Studies on the efficacy of mebendazole (single oral dose of 500 mg) conducted on Pemba Island, revealed cure rates 21 days post-treatment of 97% for *A. lumbricoides*, 23% for *T. trichiura* and 8% for hookworm in children in 1999. The egg-reduction rate achieved with mebendazole was 99% for *A. lumbricoides*, 81% for *T. trichiura* and 52% for hookworm in the same children from Pemba *(*48). A study on the efficacy of albendazole (triple oral dose of 400 mg), conducted in schoolchildren from Unguja island in 1994, revealed cure rates of 99% for *A. lumbricoides*, 43% for *T. trichiura* and 88% for hookworm three weeks post-treatment. The egg-reduction rates were 99% for *A. lumbricoides*, 92% for *T. trichiura* and 99% for hookworm *(*18).

In contrast to these findings, a recent study conducted in Unguja revealed albendazole-cure rates of only 42% and 25% for *A. lumbricoides* and *T. trichiura* infections, respectively *(*47), indicating a considerable decrease in efficacy of this drug especially against *A. lumbricoides* compared to preceding studies. A decrease in the efficacy of mebendazole against soil-transmitted helminths was reported from Zanzibar, too *(*48). These observations call for a close monitoring of the efficacy of the drugs used for mass drug administration on Zanzibar to early recognize drug resistance development in soil-transmitted helminthiasis.

Although a recent study carried out in 2 schools in Unguja in 2007 showed that prevalences and infection intensities of all soil-transmitted helminth species declined since the onset of the control programme in 1994, the prevalences of *T. trichiura*, hookworm, *A. lumbricoides* and *S. stercoralis* were still 46.6%, 21.6%, 16.9% and 10.2%, respectively *(*49).

## Safety of the benzimidazoles

On Zanzibar, multiple studies on the efficacy of mebendazole, albendazole, ivermectin and albendazole plus ivermectin have been conducted *(18-20, 45, 46, 48, 50,* 51). Actively assessed, no severe side effects were recorded for albendazole or ivermectin in a trial conducted in Unguja in 1994, and mild side effectswere of transient nature for both treatments *(*18). Although not actively assessed, no adverse events were reported after mebendazole treatment in the week following the administration of anthelminthics in Pemba *(*48). No severe adverse reactions were reported from a trial conducted in Zanzibar in 2006 to assess the safety of triple drug co-administration (albendazole plus ivermectin plus praziquantel) *(*19). The combined treatment of albendazole and ivermectin is successfully and safely applied to treat the Zanzibari population since 2001 in the frame of the GPELF *(*20). In general, the side effects of albendazole and mebendazole, at the dosage recommended for deworming, have been described as negligible and self-limiting *(*52). However, even if the single applications of albendazole, mebendazole and ivermectin are reported to be safe, to our knowledge, there are no reports on the combined treatment of mebendazole and ivermectin. Hence, the safety of the latter drug combination needs to be confirmed.

## Significance

In Zanzibar, helminth control programmes distributing anthelminthic drugs on a regular basis to schoolchildren and the whole eligible population successfully reduced the burden of soil-transmitted helminthiasis. Prevalences and infection intensities declined by more than 70% in children attending Chaani and Kinyasini primary schools in 2007 compared to children visiting the same schools in 1994 *(*49)*.* The only exception found was for *T. trichiura* infections. For this species the prevalence in the two schools in Zanzibar remained remarkably high (46.6%). One possible explanation for the persistence of *T. trichiura* infections in Zanzibar is the low efficacy of single-dose benzimidazoles against this helminth. Hence, well conducted studies on the performance of e.g. drug-combinations for the treatment of *T. trichiura* infections are needed to reduce the transmission also of this helminth.

In settings like Zanzibar, where the prevalence of soil-transmitted helminthiasis is relatively high and where anthelminthic drugs are regularly administered to large parts of the population, the risk of resistance development in worms is considerable. Because only a few anthelminthic drugs are on the market and only few are currently in the pipeline, emergence and spread of resistance must be minimized *(*53). Studies to re-assess the efficacy of anthelminthic drugs that have been used for many years and appraisal of efficacy of drug combinations are warranted as results can guide policy decisions. The development and validation of tools for the sensitive detection, monitoring and thus prevention of emerging drug resistance is recommended by WHO *(*12).

We propose to assess the safety and efficacy of the combination treatment of albendazole plus ivermectin versus mebendazole plus ivermectin versus single-dose albendazole and single-dose mebendazole against soil-transmitted helminth infections and particularly against *T. trichiura* infections in Zanzibar. The following considerations are further motivating our proposal.

First, CRs and ERRs are unsatisfactory when *T. trichiura* infections are treated with albendazole or mebendazole alone. These drugs were applied in the past decade for mass drug administrations in Zanzibar. The application of albendazole in combination with ivermectin as distributed in the frame of the GPELF is reported to be more effective in curing *T. trichiura* infections *(*35) but still *T. trichiura* prevalences are high in Zanzibar. Mebendazole is reported to have higher CR and ERR than albendazole but a combination therapy of mebendazole and ivermectin to cure *T. trichiura* infections has - to our knowledge - not been investigated so far. Second, mebendazole and ivermectin show a good safety profile when used for mono-therapy but the safety of this drug combination has net yet been assessed. Third, it is possible that after seven years of application of albendazole in the programme to eliminate lymphatic filariasis and after five years of application of albendazole in school-based treatment programmes in Zanzibar, resistance against albendazole started to develop in soil-transmitted helminth species. This possibility has not yet been investigated. Therefore it is of utmost importance to re-assess the efficacy of albendazole, mebendazole and their combinations with ivermectin to guide policy recommendations by the government of Zanzibar and the WHO in direction of which drug regimen is most efficacious and safe to apply in control programmes with the aim to reduce soil-transmitted helminth transmission and to also effectively target *T. trichiura*. Forth, closely related to investigations on drug efficacy, the evaluation of the diagnostic potential of the FLOTAC method in terms of its applicability in local laboratories and in comparison to the Kato-Katz method will contribute to the development of new tools which are needed for a sensitive diagnosis of low-intensity helminth infections.

# Goal

Our overreaching goal is to assess the current efficacy and safety of the anthelminthic drugs and drug combinations, (i) albendazole, (ii) albendazole plus ivermectin, (iii) mebendazole and (iv) mebendazole plus ivermectin, against the major soil-transmitted helminth species prevalent in Zanzibar. These are namely *A. lumbricoides*, hookworm and *T. trichiura*. Three specific objectives are related to this goal.

## Objectives

1. Efficacy and safety of albendazole and mebendazole alone and in combination with ivermectin against *T. trichiura*: We will carry out a randomized controlled trial in Kinyasini and Chaani school with the aim to compare the efficacy and safety of a single-dose treatment with albendazole (400 mg), and single-dose treatment with mebendazole (500 mg), a combination treatment with albendazole (400 mg oral dose) plus ivermectin ( 200 µg/kg oral dose) and a combination treatment with mebendazole (500 mg oral dose) plus ivermectin (200 µg/kg oral dose) against *T. trichiura.* Efficacy against other soil-transmitted helminth infections will also be determined to find out the most effective drug regimen to fight trichuriasis in particular and soil-transmitted helminthiasis in general. These results will guide policy recommendations in an appropriate way.

2. Development of resistance against albendazole/mebendazole after several years of mass-administration: To determine the current efficacy of a single-dose treatment with albendazole (400 mg single oral dose) or mebendazole (500 mg single oral dose) against *A. lumbricoides* and hookworm, to compare it to the efficacy of the drugs reported from Zanzibar in the 1990s and to shed light on a potential rise of drug resistance of *A. lumbricoides* and hookworm in Zanzibar within the above mentioned randomized controlled trial in Kinyasini and Chaani school.

3. Comparison of FLOTAC and Kato-Katz method: To compare the performance of the recently developed FLOTAC method with the Kato-Katz method applied by ‘default’ to diagnose soil-transmitted helminth infections under local conditions with the aim to determine their strengths and shortcomings in parasitological surveys and drug efficacy trials.

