# Patient inclusion and exclusion and withdrawal criteria

## Patient inclusion criteria

1. Age ≥5 years, both sexes.
2. Submission of 1 stool sample of sufficient size to perform a total of 2 thick Kato-Katz smears at the baseline parasitological survey.
3. Submission of 1 stool sample of sufficient size to perform a total of 2 thick Kato-Katz smears at the day of treatment.
4. Infection with *T. trichiura* as determined with the Kato-Katz method at the baseline survey. Additionally, also children with *A. lumbricoides* and/or hookworm infections will be included in one of the 4 treatment arms.
5. For females, not pregnant, as verbally assessed by medical personnel on the day of treatment.
6. Absence of major systemic illnesses, as assessed by medical personnel on the day of treatment.
7. No anthelminthic treatment in the past 4 weeks, as verbally confirmed by the participant at the baseline survey.
8. Written informed consent by the parent/legal guardian.

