Three to four weeks after drug administration, treated children will be given a follow-up stool container and asked to bring a fresh stool specimen the following morning for a follow up of the treatment. Upon collection of this container the children will be handed out another container and invited to bring a second stool sample the next morning.

In the last week of the study all infected study participants will be treated free of charge with the current drug of choice albendazole (400 mg) against *A.* *lumbricoides*, *T.* *trichiura* and hookworm. The subjects infected with any soil-transmitted helminth but falling under the exclusion criteria (no. 4 and 7) will be offered a treatment after termination of their illness or after pregnancy.

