# Data analysis

The following data will be available for each individual:

Name

Age

Sex

Date of treatment

Drug used

Date of follow up

Parasitological data of first stool examination (double Kato-Katz thick smear)

Parasitological data of second stool examination (double Kato-Katz thick smear and single FLOTAC)

Parasitological data of follow up (2 stool samples with 2 Kato-Katz thick smears per sample and single FLOTAC)

Data on adverse events of treatment after 3 h (acute) and 72 h (solicited).

All data will be entered twice in Microsoft Excel version 10.0 (2002 ® Microsoft Corporation) by local staff in Zanzibar. Datasets will be compared using EpiData version 3.1 (EpiData Association; Odense, Denmark), and discrepancies removed based on the original records by the PhD student ([name]) when back in Switzerland. Statistical analyses will be carried out by the PhD student with JMP version 5.0.1 (SAS Institute; Cary, NC, United States of America). The CR of the treatments and the ERR will be compared for each drug according to the results of either the Kato-Katz or the FLOTAC method or the combination of both methods.

In addition, the frequency and severity of acute and solicited adverse events of the different drug regimens will be compared. The latter analysis will try to seek differential effects according to age, sex and initial parasite load.

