# Sample size

Sample size calculations are based on the differences in CR of albendazole or mebendazole versus albendazole and ivermectin against *T. trichiura*.

The CRs of treatment with albendazole (400 mg single oral dose) and mebendazole (500 mg single oral dose) have been reported in a recent meta-analysis to be 28% (95% CI, 13%-39%) and 36% (95% CI, 16%-51%) for *T. trichiura*; 88% (95% CI, 79%-93%) and 95% (95% CI, 91%-97%) for *A. lumbricoides*; and 72% (95% CI, 59%-81%) and 15% (95% CI, 1%-27%) for hookworm infections *(*34).

The CR of the combination treatment of albendazole (400 mg single oral dose) plus ivermectin (200-400 µg/kg) as single therapy were reported from Haiti and the Philippines for the major soil-transmitted helminths and indicated to be 79.6% and 65.1%, respectively for *T. trichiura*, 100% and 78.1%, respectively for *A. lumbricoides* and 100% for hookworm infections *(38,* 55).

No relevant references on a combination therapy of mebendazole and ivermectin exist according to a recent review on the efficacy and safety of drug combinations *(*35).

Information about CR and ERR of albendazole, mebendazole and ivermectin are also available for Zanzibar. The CRs of a single dose of albendazole (400 mg) and mebendazole (500 mg) were assessed in a single-blind randomized controlled trial performed in Pemba, Zanzibar, in 1992/93 and were 10.5% and 14.2% for *T. trichiura*, 98.9% and 97.8% for *A. lumbricoides* infections and 56.8% and 22.4% for hookworm *(*51). ERRs for albendazole and mebendazole in the same study were 73.3% and 81.6% for *T. trichiura*, 99.6% and 99.3% for *A. lumbricoides* infections and 97.7% and 82.4% for hookworm *(*51).

The CR and ERR of a single dose ivermectin (200 µg/kg) were assessed in Unguja in 1994 and were 11.3% and 58.9% for *T. trichiura*, 100% and 100% for *A. lumbricoides* infections and 0% and 0% for hookworm *(*18).

The sample sizes indicated in **Table 1** were calculated in Microsoft Excel with an equation given by Fleiss *(*56):

7.85*((A1*(1-A1))+(B1*(1-B1)))/(ABS(A1-B1))^2+2/ABS(A1-B1)+2

Where A1 is the estimated CR from treatment A (e.g. albendazole or mebendazole) and B1 is the estimated CR from treatment B (e.g. albendazole plus ivermectin or mebendazole plus ivermectin).

Using a significance level of 5% to detect greater efficacy of one treatment, and a power of 80%, the following table indicates the required number of individuals **per treatment group** at different CRs:

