**Table 1: Cure rates for *T. trichiura***

**Treatment A (albendazole or mebendazole)**

| **Treatment B**  **(albendazole or mebendazole plus ivermectin)** | 15% | 20% | 30% | 35% | 40% | 45% | 50% | 55% |
| --- | --- | --- | --- | --- | --- | --- | --- | --- |
| 60% | 21 | 27 | 48 | 69 | 106 | 185 | 407 | 1573 |
| 65% | 17 | 21 | 36 | 48 | 69 | 105 | 182 | 395 |
| 70% | 14 | 18 | 28 | 36 | 48 | 67 | 102 | 175 |
| 75% | 12 | 15 | 22 | 27 | 35 | 47 | 65 | 97 |
| 80% | 10 | 12 | 18 | 21 | 27 | 34 | 44 | 61 |
| 85% | 9 | 10 | 14 | 17 | 21 | 25 | 32 | 41 |
| 90% | 8 | 9 | 12 | 14 | 16 | 20 | 24 | 29 |

Based on the given information we estimate the CR of albendazole/mebendazole for *T. trichiura* infections to be between 20% and 45% and the CR of the combination of albendazole/mebendazole plus ivermectin to be between 65% and 80%. Hence, a sample size of at least 105 participants per treatment group is needed for significance analysis.

In the proposed study sites, the prevalence of *T. trichiura* infections is most likely to be above 30% and the compliance is estimated to be around 90%. These assumptions are based on a study performed in Kinyasini and Chaani schools in 2007 where 25.9% of the children were found to be infected with *T. trichiura* after examination of 1 stool sample and 47.9% after examination of 3 stool samples with the Kato-Katz method and where the compliance to submit 1-3 stool samples was >85%. In view of the required number of cases per group, and allocating for patients lost to follow-up, at least 2000 subjects would have to be screened so that 500-600 infected individuals infected with *T. trichiura* can enter the trial (see Appendix 5).

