**Week 9 and 10**

- Distribute labelled stool container to all children treated in the randomized trial

- Collect filled stool containers from all children and transport them to the laboratory, distribute a labelled new stool container for every one that was collected until each child submitted 2 stool samples after treatment

- Prepare 2 Kato-Katz smears from each stool sample and examine as described beyond until 2 consecutive stool samples from all children included into the trial were examined with the Kato-Katz method

- Preserve 1 g of 1 stool sample in a labelled container with 10ml SAF from the sub-sample of children randomly selected to be examined with FLOTAC and which finally entered the trial

- Inform participants in person about the parasitological diagnosis

- Treatment of all participating school-children free of charge with albendazole by members of the national helminth control team

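### Objective 2 compares current cure rates with 1990s Zanzibar rates without matching the number of stools and smears, so a difference may reflect sampling effort rather than resistance, in a direction the documents do not settle

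*Combined protocol and SAP*

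**What the plan says.** Objective 2 (Objectives) concerns how well a single dose of albendazole or mebendazole now works on hookworm and A. lumbricoides. What the plan intends to do with that result is "to compare it to the efficacy of the drugs reported from Zanzibar in the 1990s". The stated purpose of setting the two periods side by side is "to shed light on a potential rise of drug resistance of" these two parasites.

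Follow-up sampling is two stools per child. Field procedures, on the first follow-up container: "Upon collection of this container the children will be handed out another container and invited to bring a second stool sample the next morning". Appendix 3 (Week 9 and 10) has containers reissued "until each child submitted 2 stool samples after treatment". The Data analysis section lists the follow-up data as "2 stool samples with 2 Kato-Katz thick smears per sample and single FLOTAC".

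Before treatment there are also two stools. One is taken at the screening survey. The other is inclusion criterion 3: "Submission of 1 stool sample of sufficient size to perform a total of 2 thick Kato-Katz smears at the day of treatment".

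Study type and measurement makes both the cure rate and the egg reduction rate primary. Its cure-rate formula counts children positive at baseline and at 3-4 weeks. It does not say which pre-treatment stool defines baseline positivity or how the two follow-up stools are combined.

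The Data analysis section gives no method for the historical comparison. The 1990s rates, in Helminth control programmes in Zanzibar and in Sample size, are given without the number of stools or smears behind them.

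**The concern.** A child counts as cured when no eggs are found, so the observed cure rate depends on how hard one looks. The plan accepts this. Its section on control of soil-transmitted helminths says that Kato-Katz misses light infections. Below Table 1, T. trichiura positivity in the same two schools in 2007 is given as 25.9% "after examination of 1 stool sample and 47.9% after examination of 3 stool samples with the Kato-Katz method".

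The randomised comparisons are protected because all four arms are sampled alike. Objective 2 has no such protection, since it rests wholly on comparability with outside studies. If sampling effort differs, the cure rate moves with no change in the drug. The protocol says its results are meant to guide policy in Zanzibar and at WHO. Its background already reads a lower albendazole cure rate in a recent study as a considerable loss of efficacy.

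**Working it through.** The plan gives no figure for Objective 2 to reproduce. Its only sample-size result, 105 per group at 45% versus 65%, does reproduce: 7.85 × (0.2475 + 0.2275)/0.04 + 2/0.20 + 2 = 105.2. It concerns T. trichiura between arms and has no bearing here.

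**Inputs from the documents.** The 1992/93 Pemba trial (Sample size) gives cure rates for albendazole and mebendazole of "56.8% and 22.4% for hookworm", and of 98.9% and 97.8% for A. lumbricoides. Current follow-up is two stools.

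**Assumptions.** The comparator used one follow-up stool (not in the documents). Stools are independent, with the same per-stool sensitivity s for both drugs. A child is positive if any smear is positive. True efficacy is unchanged. Differences in smears per stool are not modelled.

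**Model.** With u the true proportion not cured, the observed cure rate on k stools is CR_k = 1 − u[1 − (1 − s)^k]. Going from one stool to two therefore lowers it by (1 − CR_1)(1 − s).

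**Constraint on s.** Because u cannot exceed 1, s must be at least 1 − CR_1. Mebendazole against hookworm gives s ≥ 1 − 0.224 = 0.776.

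**Albendazole, hookworm (56.8% on one stool):**
- s = 0.776: fall 0.432 × 0.224 = 9.7 points, reads 47.1%
- s = 0.8: fall 0.432 × 0.2 = 8.6 points, reads 48.2%
- s = 0.9: fall 0.432 × 0.1 = 4.3 points, reads 52.5%

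**Mebendazole, hookworm (22.4%):** at s = 0.8 the fall is 0.776 × 0.2 = 15.5 points (reads 6.9%); at s = 0.9 it is 7.8 points (reads 14.6%).

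**A. lumbricoides, at s = 0.776:** albendazole 0.011 × 0.224 = 0.25 points; mebendazole 0.022 × 0.224 = 0.5 points.

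**Other comparator sampling.** With two comparator stools the shift is zero. With three, CR_2 = 1 − (1 − CR_3) × [1 − (1 − s)²]/[1 − (1 − s)³]. The 2007 T. trichiura figures give s/[1 − (1 − s)³] = 25.9/47.9, so s = 0.451. Used as a stand-in for hookworm, the ratio is 0.699/0.835 = 0.837, and 56.8% would read 1 − 0.432 × 0.837 = 63.8%, 7 points higher. This s is allowed in the three-stool case, since 0.835 exceeds the required 0.776. At s = 0.9 the reading would be 57.2%. Either way the shift would offset part of a real decline.

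**The case against.** The strongest objection is that existence and direction rest on sources outside the documents. That stands: the 1990s stool numbers are not given, and with two stools there is no artefact.

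A reader might apply the 45% per-stool sensitivity from the 2007 figures to a one-stool comparator and infer that albendazole hookworm cure would drop from 56.8% to 33.1%, a spurious fall of 24 points. The documents do not support this. At s = 0.45 no one-stool cure rate can be below 55%, yet the same Pemba trial reports 22.4% for mebendazole against hookworm. For T. trichiura, the species that gave the 45%, it reports 10.5% and 14.2%, which need s of at least 0.895 and 0.858. The inference would also mean a true albendazole cure of about 4% (1 − 0.432/0.451) beside a reported egg reduction of 97.7%. Falls of 17 or 13 points, from s = 0.6 or 0.7, fail on the same constraint.

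Three further limits stand:
- The plan does not make cure rate alone the test of resistance. Objective 2 speaks of efficacy, and the egg reduction rate is also primary. No effect on that rate was calculated.
- If both pre-treatment stools define infection, added light infections may be easier to cure and could partly offset a fall. Matching follow-up stools alone could then bias the comparison the other way.
- Objective 2 is modest in its wording, and for A. lumbricoides, half of its scope, sampling effort hardly matters. It could not explain a fall to the 42% cited in the background.

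**Conclusion.** The concern holds as an unmatched, unspecified comparison of unknown direction. It is not a demonstrated bias towards resistance: a reader might infer that two follow-up stools must make the current cure rate lower than the 1990s rates, but that follows only if the comparators examined fewer.

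Conditional on a one-stool comparator, independent stools and constant sensitivity, the spurious fall for albendazole against hookworm is about 4 to 10 points (s from 0.9 to 0.78), and under 1 point for A. lumbricoides. The upper limit depends on sensitivity being equal after both drugs. If it were lower among albendazole failures the fall could be larger, but the documents give no figure for that. A shift of this size could be misread in a historical comparison. The randomised comparisons are unaffected.

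**What to change.** In Objective 2 and the Data analysis section:

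- State, for each 1990s comparator, the pre-treatment and follow-up stools and smears examined. The sponsor can look these up in the papers it cites.
- State which pre-treatment stools define baseline infection and how the two follow-up stools are combined.
- For Objective 2, compute the cure rate and egg reduction rate from the same number of stools and smears as the comparator, before and after treatment, where samples A to D allow it (for example, one stool before and the first stool after). Report the full-sample rate beside it.
- Keep full sampling for the between-arm comparisons.
- Where a comparator's sampling is unknown or cannot be matched (for example, three follow-up stools), say so, and do not read a difference in cure rate alone as evidence for or against resistance.
- List the mismatches that remain, such as the triple dose in the 1994 Unguja albendazole study and Pemba versus Unguja, as limits of the comparison.

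The cost is a few sentences and one extra tabulation. Appendix 5 already logs samples A to D in separate columns, so no fieldwork changes. Settling the rule beforehand also prevents choosing between the two rates after the results are seen.
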